### Recruitment

Local agents (the government Regional Nutrition Office and the local NGOs) will carry out the initial recruitment of communities by introducing the ECD curriculum structure and scope. At this time, CHWs (two per community) will indicate whether they would be willing to participate in a two-week training session and implement the ECD group sessions in their community for a one-year period and participate in monthly surveys. If a CHW declines to participate, a replacement community will be chosen. Informed consent for the administration of the survey will be collected by the local agents after this introduction to the planned activities and will be collected again more formally by the survey firm at baseline, after the training has occurred.

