##### Fidelity

CHWs and their NGO supervisors will receive training before the launch of the interventions. Training will include discussion of notion of child development, the importance of early stimulation, the content of the curriculum, with emphasis of role-play content, and assessments of comprehension. An in-person three-days coaching is planned at the onset of the activities and refresher sessions to reinforce concepts and ensure consistent quality across implementers are planned every 4–6 months. In addition, coaches from the ECD team in Madagascar will be available by phone monthly for monitoring and support, and CHWs will have access to phones for technical support.

The NGO supervisors will administer a monthly group session checklist, adapted from the Reach-Up material to assess the quality of the sessions being carried out. Finally, we will develop a brief tracking tool to be used by CHWs to record any changes in toy/play material inventory (losses, deterioration in quality) over time.

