#### Community surveys

Surveys will be conducted with two key informants (e.g. mayor, community chief, teachers, doctor, religious leaders, etc.) in each community on a monthly basis to obtain information about key community infrastructure, ongoing programs and events, the frequency and duration of local economic/weather/other shocks, and information on market access, and prices of key commodities. Key informants are identified by the CHWs in collaboration with the supervisors. Data collected from these surveys will be used to control for community-level time-varying socio-economic shocks during the study period that may affect our key outcomes of interest.

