### Outcomes

The following primary and secondary outcomes will be collected:•*CHW time allocation* (Primary outcome), measured through a 24-h recall of time spent on program related tasks (group nutrition sessions, home visits, treatment of illnesses, administrative tasks, ECD group sessions, and toy maintenance), household chores, productive activities, caregiving and rest/social activities. This will be measured at baseline and monthly for 12 months through phone-surveys.•*CHW psychosocial wellbeing* (Secondary outcome), measured through the monthly phone surveys. Motivation and depression will be measured at baseline and every four months using the short-form Center for Epidemological Studies Depression Scale (CES-D) [23] and motivation scales [24] adapted to the Malagasy context and the Rosenberg Self-Esteem Scale [25]. Perceived stress will be measured monthly using the Perceived Stress 7-Item Scale (PSS-7) [26].•*Caregiver-child dyad participation in health and nutrition activities* (Primary outcome), measured through the administrative data monthly. The range of program activities that are collected range from monthly attendance to group promotion sessions and growth monitoring sessions, indicators of whether they received home visit in last month, and whether they received vitamin A supplementation, deworming and vaccinations (age-specific).•*Caregiver-child dyad participation in ECD sessions* (Primary outcome), measured through the administrative data monthly. Information ranges from number of ECD sessions attended by caregiver-child dyad in last month and whether the children transitioned from one age group to the subsequent one.

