#### Empirical specification

We have two primary estimating equations, which we discuss below. The first (Eq. 4) is our main specification for comparisons between each intervention arm and the control group (Primary Questions 1 & 2, Secondary Question 1). These models will be used to estimate the impact on CHW outcomes (time use and motivation) and caregiver-child dyad outcomes (participation and engagement). All specifications will control for the method of randomization by including strata indicator variables, month fixed effects to account for time-varying unobservable (to the researcher) factors, and correcting standard errors for clustering at the community level. For clarity, we reproduce one set of equations here, but they can be applied to either CHW-level or caregiver-child dyad-level analysis.

Let the outcomes of interest will be represented by $${Y}_{ijt}$$, where the subscript refers to CHW (or caregiver-child dyad) *i*, in community *j*, at time *t*.

The main ITT impact of each intervention arm on the outcome of interest is estimated as follows:4$${Y}_{ijt} = \alpha + {\beta }_{1}{T}_{j} +{\beta }_{2} {{T}_{+}}_{j}+ \gamma {Y}_{ij0} + {\delta }_{1}{X}_{ijt}+ {\delta }_{2}{V}_{jt}+ {\theta }_{s}+ {\lambda }_{t} + {\varepsilon }_{ijt}$$

where $${T}_{j}$$ or $${{T}_{+}}_{j}$$ are indicators for the random assignment of community j to treatment, $${Y}_{ij0}$$ are baseline outcomes for CHW (or caregiver-child dyad) i (ANCOVA specification), $${X}_{ijt}$$ are CHW-level (or caregiver-child level) covariates (e.g. age, gender, education level), are $${V}_{jt}$$ are time-varying community-level characteristics (e.g. shocks, prices/wages), $${\theta }_{s}$$ are strata fixed effects (randomization triplet fixed effects), $${\lambda }_{t}$$ is a set of month fixed-effects, and $${\varepsilon }_{ijt}$$ are error terms clustered at the community level.

β_1_ and β_2_ represent the average impact of being assigned to T or T + over 12- and 6-month periods, respectively, relative to the control group. Testing primary question 1 and primary question 2 is equivalent to testing whether (H0: β_1_ = 0 and (H0: β_2_ = 0).

To address Primary Question 3, we restrict the sample to the communities that are offered any ECD intervention (T or T +) and estimate the following equation:5$${Y}_{ijt} = \alpha + {\beta }_{2} {{T}_{+}}_{j}+ \gamma {Y}_{ij0} + {\delta }_{1}{X}_{ijt}+ {\delta }_{2}{V}_{jt}+ {\theta }_{s}+ {\lambda }_{t}+ {\varepsilon }_{ijt}$$

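### The CHW baseline is surveyed after the ECD training, yet Eq. 4 adjusts CHW outcomes for it as if it were pre-treatment

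*Protocol article*

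**What the plan says.** Recruitment asks the CHWs (two per community) whether they are "willing to participate in a two-week training session and implement the ECD group sessions in their community for a one-year period". It then says that consent for the survey "will be collected again more formally by the survey firm at baseline, after the training has occurred". This places the survey firm's baseline after the training.

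The training itself appears under Study arms, Treatment (T), Fidelity: "CHWs and their NGO supervisors will receive training before the launch of the interventions". The control arm is described as the status quo programme, with no training mentioned. Sampling, stratification and randomization states that participants cannot be blinded to their assignment.

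The Outcomes section takes the CHW measures from this survey. Of time allocation it says "This will be measured at baseline and monthly for 12 months through phone-surveys". Of the psychosocial scales it says "Motivation and depression will be measured at baseline and every four months", with perceived stress measured monthly.

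Empirical specification, Eq. 4, includes the term gamma x Y_ij0 for the baseline outcome (ANCOVA). Parameters of interest gives improved precision as the reason for including it.

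**The concern.** Baseline adjustment in a randomized trial gains precision without bias because allocation cannot have changed the baseline. That condition is in doubt here. On the likelier reading, CHWs in the ECD arms have been through up to two weeks of curriculum training and know that they will run the group sessions before their baseline is recorded, while control CHWs have not.

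Secondary Question 1 asks how integrating ECD affects CHW wellbeing. Training and the prospect of added duties could plausibly shift motivation, self-esteem, depression and stress. If they do, part of the effect sits in Y_ij0, and Eq. 4 removes a fraction gamma of it from beta1 and beta2. The adjusted coefficient is then no longer the full effect of assignment.

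**Working it through.** **Inputs from the article (Power calculations):** autocorrelation 0.5 or 0.7; one baseline and 11 follow-ups; effect size 0.5 SD; 80% power; ICC up to 0.3; two CHWs in each of 25 communities per arm, so 50 CHWs per arm. **Assumed:** two-sided alpha 0.05 (not stated), and delta, the shift in Y_ij0 caused by training in the ECD arms, for which the article gives no figure. I use 0.1 to 0.3 SD. The autocorrelations are given for time allocation; applying them to the psychosocial scales is also an assumption.

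**1. Reproduce Table 1.** With r follow-ups and the same rho between baseline and follow-up as between follow-ups, the ANCOVA variance factor is f = (1 + (r-1) rho)/r - rho^2.
- For r = 11, f = 0.2955 at rho 0.5 and 0.2373 at rho 0.7.
- n = 2 x (2.80/0.5)^2 x f = 18.55, rounded to 19, and 14.90, rounded to 15.
- Multiplying by 1.2 and 1.3 and rounding up gives 23 and 25 (rho 0.5), and 18 and 20 (rho 0.7).

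All six cells match, so the plan's power rests on this baseline adjustment, with gamma = rho.

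**2. Effect of a shifted baseline.** If the true effect on the follow-up mean is tau and training has moved Y_ij0 by delta, ANCOVA estimates tau - gamma x delta.

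| delta (assumed) | shift at gamma 0.5 | shift at gamma 0.7 | share of 0.5 SD |
|---|---|---|---|
| 0.1 SD | 0.05 | 0.07 | 10-14% |
| 0.2 SD | 0.10 | 0.14 | 20-28% |
| 0.3 SD | 0.15 | 0.21 | 30-42% |

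Simulation with tau = 0.5 and delta = 0.2 returned 0.403 (rho 0.5) and 0.359 (rho 0.7), against 0.40 and 0.36 from the formula. With delta = 0 it returned 0.501 for both. The 0.5 SD benchmark is the plan's figure for time allocation; the article gives none for the psychosocial scales.

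**3. Power.** With 50 CHWs per arm, ICC 0.3 and delta 0.2 of the same sign as a 0.5 SD effect, power falls from 98-99% to about 90%.

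**4. Price of leaving Y_ij0 out.** The term -rho^2 drops from f. MDE = 2.80 x sqrt(2 x f x 1.3/50) at rho 0.5 and ICC 0.3.
- Monthly stress, r = 11: f goes from 0.2955 to 0.5455, and the MDE from 0.35 to 0.47 SD.
- Four-monthly scales, about r = 3 over 12 months: f goes from 0.4167 to 0.6667, and the MDE from 0.41 to 0.52 SD.

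**The case against.** **Training of controls is not stated.** Recruitment asks about willingness to train before any arm is mentioned, no section says when arms are disclosed, and the flow figure is not available here. If every CHW was trained, the contribution of training to delta would be near zero. This stands as a limit: the treatment-only reading is the likelier one, but it is an inference. The baseline timing also appears only in a sentence about consent.

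**Training precedes the sessions.** One could say that a baseline after training but before launch isolates the effect of the sessions. ANCOVA does not deliver that either. With tau 0.5, delta 0.2 and gamma 0.5, the full effect is 0.50, the change from the post-training baseline is 0.30, and Eq. 4 returns 0.40, which is neither.

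**Reach is narrow.** This stands. Dyad participation comes from administrative registries. Session time, the main route to a change in 24-h recall, does not yet exist at baseline. The same training is described for T and T+, so the contrast between them is not implicated.

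**Direction is open.** This stands. If training raises motivation and later workload lowers it, adjustment pushes the estimate away from zero. A reader who infers dilution in every case goes too far.

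**A stronger reading concerns X_ijt and V_jt.** A reader might infer that these covariates also adjust part of the effect away, since they carry a time index and the V terms "are time-varying community-level characteristics (e.g. shocks, prices/wages"). The article does not support this. The named covariates are age, gender, education, shocks, prices and wages; ECD group sessions would not plausibly change them, wages at most marginally. The community survey does "obtain information about key community infrastructure, ongoing programs and events", but that is survey content and not a stated covariate; the stated use is control for socio-economic shocks. Nor are informants chosen by treated CHWs alone: "Key informants are identified by the CHWs in collaboration with the supervisors", and this applies in every arm.

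**Conclusion.** The point holds for the CHW survey outcomes, mainly motivation, self-esteem, depression and stress under Secondary Question 1, and to a lesser degree for time use under Primary Question 1. The plan adjusts for a baseline that allocation may already have shifted. The resulting bias is -gamma x delta, or 0.05-0.21 SD in absolute size for gamma 0.5-0.7 and delta 0.1-0.3 SD, with its sign depending on whether delta and the later effect agree.

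This rests on three assumptions: that only ECD-arm CHWs were trained before baseline, that training or knowledge of the new duties moves the scales, and that the plan's autocorrelations carry over to them. If delta is zero there is no bias. The 25 clusters per arm and the participation analyses are unaffected.

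**What to change.** State, by arm, when the CHW baseline fell relative to training and to disclosure of the assignment. The baseline should be taken before both. Trial status describes data collection as ongoing until March 2022, so for this trial the analysis changes below are probably the ones still open.

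Where the baseline followed training in the ECD arms only:
- report the arm difference at that visit as an early effect, not as a balance check;
- estimate the psychosocial effects without Y_ij0, keeping strata and month effects and covariates fixed before allocation, and present this alongside the ANCOVA result;
- show the time-use results with and without Y_ij0.

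If all CHWs were trained before baseline, saying so largely settles the training component and Eq. 4 can stay as written.

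No new data are needed. The cost is the lower precision of the models without Y_ij0, as worked out above: roughly 0.11 to 0.12 SD on the MDE at rho 0.5 and ICC 0.3.

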### Study arms

#### Control: status quo health and nutrition program

The standard of care program is a community-based health and nutrition program managed by U-PNNC (Unité—Programme de Nutrition Communautaire). The program has a package of activities that address maternal and child health and nutrition (MCH&N) issues:•Health: child health monitoring, integrated management of non-severe child illness, pregnancy monitoring•Nutrition: growth promotion, breastfeeding promotion and complementary feeding education, monitoring of pregnant and lactating women, oral rehydration therapy for treatment of severe diarrhea and management of moderate and acute malnutrition

Activities are carried out at the community level by two CHWs, who are elected by the community.

#### Treatment (T): Status quo health and nutrition program + Fortnightly group ECD sessions, based on Reach Up and Learn curriculum and behavioral supporting nudges

##### Community mobilization/information campaign

At the onset of the program, the ECD activities will be presented to the treatment communities during community mobilization campaigns by the program supervisors and the CHWs, supported by local authorities. The mobilization will start with an introduction that raises awareness about the importance of ECD and explains the objectives of the program. It will be followed by a description of the eligibility, enrollment, structure/content of the sessions, and time commitment by the caregiver-child dyads. The dissemination will be supported by photos and videos of the sessions carried out during pre-tests, as well as supporting materials used during the sessions. We may consider selecting individuals within each neighborhood who would be best placed to spread information about the intervention to encourage adherence and elicit possible interest in enrollment.

##### Household recruitment

During these mobilization campaigns, NGO supervisors will collect names from all eligible households who are interested in participating in the ECD sessions. To be eligible for the ECD curriculum, households must have a child between 6–30 months, have a primary caregiver that is willing to participate in the group activities and live in the selected community. Households or caregiver-child dyads could also register with the CHWs or NGO supervisor during the two weeks following the mobilization campaign.

On average, there are about 100 age-eligible mother–child dyads registered in the health and nutrition program in the target communities, and the interventions will be provided for less than half of this eligible number (maximum 40). If there is more demand than can be accommodated for a given age group at a community, all interested households will be entered into a non-public lottery. The research team will randomly draw 10 households from this list to offer a spot in the ECD program, with the remainder being added to a wait list, and will send the final list to the NGO supervisor. Households who are on the wait list will be informed that they have been added to a wait list due to limited space in the program. If enrolled participants do not attend three consecutive ECD sessions (out of the 12 session planned over a period of six months), randomly selected households from the waitlist will be offered to join. There are no additional screening criteria.

##### ECD group sessions

The program will consist of fortnightly group sessions (one to one and a half hour on average) of 10 caregiver-child dyads per six-month age group, for a total of 12 sessions per age group over a period of six months. With four age groups of 10 children each (from 6 to 30 months old), coverage can reach up to 40 children at any given time. Each session is expected to require half a day of the CHW’s time for preparation, administration, filling out of registries, and clean up.

The Reach Up and Learn ECD stimulation curriculum was adapted to a group setting based on the previous MAHAY experience. A session will start by (i) reviewing the previous sessions activities and themes, with a few questions to reinforce the messages, followed by (ii) a discussion among program participants. The CHW will then introduce a theme and message for the session. (iii) a pledge will then be recited by all caregivers and CHWs, highlighting the importance of the caregiver’s commitment. (iv) Caregivers will be grouped in twos or threes to discuss the stimulation activities they did with their own child since the last session. Children and caregivers will spend in total 20 to 30 min on 3–4 play activities using age-appropriate toys. Then, they will all learn a new song to sing with or to the child. (v) The session will end with feedback on the messaging and the distribution of a reminder sheet with the main messages, play activities, lyrics of the song, a list of activities to do at home before the next session, followed by (vi) a closing song.

The age-appropriate play materials used during the group ECD sessions have been adapted from the Reach Up and Learn program’s list. They have been adapted to the materials available in Madagascar. The production and maintenance of the play materials is carried out by a team of trained volunteer youth groups (scouts) (Tily Eto Madagasikara, TEM) in partnership with U-PNNC.

Behavioral nudges will be incorporated into the ECD group sessions to promote peer support and encourage sustained caregiver-child play in between the fortnightly meetings. These nudges will include a little paper booklet (memory aids) that recap the main lessons of the session with pictures and short messages, the lyrics of the song learned and the activities done during the session, and provide suggestions for small feasible actions that can be taken at home to promote learning and child development. Caregivers are instructed to fill in the check-boxes listing the activities they have completed with their child at home and bring back the memory aid to the subsequent group session to share their progress in pairs. These memory aids complement the ECD sessions through light-touch reminders to play, and they can be used to reinforce concepts in between sessions and teach other family members so they can also put the lessons into practice. At the end of the curriculum, each caregiver-child dyad that attended each session will have a complete set of memory aids that recap all the ECD lessons learned. A recent study in Zambia suggests that low-cost visual reminders in the home about target activities to promote child development and nutrition may have positive effects, particularly for the most vulnerable [22].

##### Transitions across age groups

The study period will cover two cycles of the 12 ECD group sessions. After six months, participants of the first three age groups will be offered to “graduate” to the next age group’s curriculum, and new participants will be added to the youngest age group. At this time, if there are participants who decide not to move to the subsequent age group cycle at the transition point, wait list participants will be randomly offered a spot in the age group.

##### Fidelity

CHWs and their NGO supervisors will receive training before the launch of the interventions. Training will include discussion of notion of child development, the importance of early stimulation, the content of the curriculum, with emphasis of role-play content, and assessments of comprehension. An in-person three-days coaching is planned at the onset of the activities and refresher sessions to reinforce concepts and ensure consistent quality across implementers are planned every 4–6 months. In addition, coaches from the ECD team in Madagascar will be available by phone monthly for monitoring and support, and CHWs will have access to phones for technical support.

The NGO supervisors will administer a monthly group session checklist, adapted from the Reach-Up material to assess the quality of the sessions being carried out. Finally, we will develop a brief tracking tool to be used by CHWs to record any changes in toy/play material inventory (losses, deterioration in quality) over time.

##### Treatment Plus (T +): Status quo health and nutrition program + fortnightly group ECD sessions, based on Reach Up and Learn curriculum and behavioral supportive nudges + individual toy boxes with age-appropriate toys for home-based play

After six months of program operation, half of the ECD communities will be randomly allocated to receive an enhanced play materials and activities package for home use to complement the Reach Up and Learn curriculum (T +) (Fig. 2). To promote sustained play between group sessions and daily practice, participating families will receive age-appropriate toy/books boxes at the start of the 6-month cycle. This toy box is composed of one developmentally-appropriate toy given as a gift to the caregiver-child dyad and kept at home. In addition, caregiver-child dyads will be able to borrow a toy and a book from the ECD group session play activities every two weeks to increase play variety and to practice activities learned with the CHWs. Caregivers will learn how to use the toys to play with their children, with lessons at each meeting providing scaffolding to encourage developmental growth. The 6-month delay in implementing T + increases the power to detect CHW time cost differences from integrating ECD group activities (T) with the health and nutrition program, while maintaining sufficient power to detect differences in take up related to the enhanced play materials (T +) by the caregivers (see section Power Calculations).

